#### 10.4.1.3. P300 ERP

Participants are seated with the EEG cap and headphones on and are instructed to sit still and relax and to keep their eyes closed. During the task, participants are being presented with two types of auditory stimuli (“standards” and “deviants”). Both stimuli last 100ms and have the same sound pressure level (85dB) and the same 5ms rise and fall times. The standard and

deviant stimuli have a tone frequency of 500 Hz and 2000 Hz, respectively. For each acquisition the number of deviant stimuli is randomly selected between 25 and 35. The number of standard stimuli is adjusted to have 15% of deviant stimulus frequency. Each interstimulus interval is set randomly and can take values between 1200 and 1900ms. Due to the random number of stimuli the task might last from 5 to 7 minutes (instructions included). Participants must pay attention to the tones and count the infrequent/deviant tones.

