#### 4. OBJECTIVES AND ENDPOINTS

|                  | Objective                                                                                                                               | Endpoint                                                                                                                                                                                                                                                                                                                                                                                                                                                                                                                                          |
|------------------|-----------------------------------------------------------------------------------------------------------------------------------------|---------------------------------------------------------------------------------------------------------------------------------------------------------------------------------------------------------------------------------------------------------------------------------------------------------------------------------------------------------------------------------------------------------------------------------------------------------------------------------------------------------------------------------------------------|
| Primary   | To compare the quantitative performance in terms of signal quality between three new EEG systems and a standard clinical wet EEG system | 
 
- EEG features derived from resting state recordings
 
- Latencies and amplitudes of evoked components as well as Signal-to-Noise Ratio from an auditory oddball task
 
- Visual gamma activity (e.g. power and peak frequency)
 
- Test-retest reliability of all EEG derived features during resting state and task recordings
 
- Robustness to artefacts and non-neural signal sources
 
                                                                          |

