#### Derived endpoints

- Peak latency and amplitudes of sensory (e.g. N100) and cognitive (e.g. P3b) evoked potentials from the auditory oddball task as well as topographic scalp distributions of the evoked components;

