#### Statistical analysis

- Univariate statistics and linear modelling to assess differences in derived endpoints and scalp topographies between the test devices and the gold-standard clinical wet system.

- Multivariate analyses to decode frequent from infrequent tones for each device as well as a comparison of decodability of frequent and infrequent tones between the test devices and the gold-standard clinical wet system.

- Correlational statistics (e.g. intra-class correlation) to assess test-retest reliabilities (D1 to D8) for derived endpoints and scalp topographies for each device as well as univariate/resampling statistics to assess differences in test-retest reliabilities between devices.

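### Scoring the P300 task by peaks lets a noisier device record a larger amplitude from the same brain response

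*Protocol*

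**What the plan says.** Section 4 of the Protocol lists among the primary endpoints "Latencies and amplitudes of evoked components as well as Signal-to-Noise Ratio from an auditory oddball task". Section 10.4.2 then says how components are scored. Under P300 ERP, derived endpoints, it names "Peak latency and amplitudes of sensory (e.g. N100) and cognitive (e.g. P3b) evoked potentials from the auditory oddball task" and the scalp topographies of those components. No other amplitude measure is named, and SNR is not defined.

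The planned comparison is "Univariate statistics and linear modelling to assess differences in derived endpoints and scalp topographies between the test devices and the gold-standard clinical wet system". Test-retest reliability of the same scores and "a comparison of decodability of frequent and infrequent tones between the test devices and the gold-standard clinical wet system" are planned as well.

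Section 10.4.1.3 sets the number of trials. "For each acquisition the number of deviant stimuli is randomly selected between 25 and 35", and "The number of standard stimuli is adjusted to have 15% of deviant stimulus frequency". The count is drawn again for each of a participant's eight runs (four devices, two visits). The Synopsis, under criteria for evaluation, also plans to quantify and compare the usable artefact-free data for every recording.

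**The concern.** The study asks whether the devices deliver comparable signal quality, so noise is expected to be one of the things that differs between them. A peak score takes the largest value in a search interval and so collects whatever noise happens to lie on top of the component. The amplitude endpoint then mixes two quantities: how much of the brain response the device transmits, and how noisy its average is. Because they act in opposite directions, a device that both attenuates the response and adds noise can look close to the wet reference. A device that transmits the response faithfully but is noisier can appear to differ from it. In either case the amplitude contrast does not mean what its label says. Averages of 25 to 35 deviants, before any rejection, are too short for residual noise to be ignored.

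**Working it through.** **Task length, the Protocol's own figure.** Inputs from Section 10.4.1.3: 25 to 35 deviants, a 15% deviant share, "Each interstimulus interval is set randomly and can take values between 1200 and 1900ms", and "Both stimuli last 100ms".

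- Tones per run: 25/0.15 = 167 to 35/0.15 = 233.
- Mean interval: (1200 + 1900)/2 = 1550 ms. Counted onset to onset, 167 × 1.55/60 = 4.3 min and 233 × 1.55/60 = 6.0 min.
- If the 100 ms tone is added to each interval: 4.6 and 6.4 min.
- With about 0.4 to 0.7 min of instructions (assumed), the second variant gives about 5 to 7 min, which agrees with the stated duration. The trial numbers are therefore taken as they stand.

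**Direction of the bias.** Write the average of n deviants as y(t) = s(t) + r·z(t). Here s is the true response with its peak at t0, z is zero-mean noise of unit SD, and r = SD/√n is the residual noise.

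- The maximum of y is never below y(t0), so its expectation is at least s(t0). The peak is biased upward.
- The expected maximum is convex in r and smallest at r = 0, so it cannot fall as r rises. More single-trial noise or fewer trials pushes it up.
- For a negative component such as N100, the same holds with the sign reversed.

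**Size.** The Protocol gives no amplitude, noise level or search interval, so these are assumed. Setting 1: noise 0.5 to 20 Hz, peak searched from 250 to 500 ms. Setting 2: Gaussian component at 380 ms with 60 ms width, noise low-passed at about 10 Hz, peak searched from 250 to 600 ms, mean window 330 to 430 ms.

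| Setting | True peak (µV) | Single-trial SD (µV) | n | r = SD/√n | Mean scored peak (µV) |
|---|---|---|---|---|---|
| 1 | 8 | 10 | 30 | 1.83 | 9.7 |
| 1 | 8 | 15 | 30 | 2.74 | 10.9 |
| 1 | 8 | 15 | 20 | 3.35 | 11.8 |
| 2 | 10 | 10 | 30 | 1.83 | 11.2 |
| 2 | 10 | 20 | 30 | 3.65 | 13.5 |
| 2 | 5 | 20 | 30 | 3.65 | 9.6 |

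- Same response, more noise: 10.9/9.7 = 1.12, or 1.14 with the 9.6 µV that a repeat run gave for the first row. That is about 13%.
- More noise and fewer trials: 11.8/9.7 = 1.22, about 20%.
- Noise doubled in setting 2: 13.5/11.2 = 1.21, about 20%.
- Masking in setting 2: a device that halves the response (10 to 5 µV) and doubles the noise scores 9.6 against 11.2. That is about 15% lower, where the true loss is 50%.
- Mean in a fixed window: bias of 0.00 to 0.02 µV in setting 2 at every noise level (SD 8 to 30) and count (25 to 35) tried. In setting 1 it is 6.83 µV in both the first and third rows, against a true 6.84.
- Peak latency in setting 2, true 10 µV, n = 30: scatter rises from about 23 ms at SD 10 to 41 ms at SD 20.

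**The random count, taken separately.**

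- Extreme pair of runs: √(35/25) = 1.18, or 20·log10(1.18) = 1.46 dB, in the SNR of an average.
- Uniform 25 to 35: SD of the count 3.16; CV of √n about 5.3%.
- Between devices, with 32 × 2 = 64 runs each: standard error of the difference in mean count = 3.16 × √(2/64) = 0.56 trials. That is 0.56/30 = 1.9% of the count, or about 0.9% (0.08 dB) in SNR.
- Effect on the peak bias of 25 against 35 trials (setting 2, true 10 µV): 1.43 − 1.11 = 0.32 µV at SD 10, and 3.94 − 3.09 = 0.85 µV at SD 20.

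**The case against.** - **The scoring detail belongs to the SAP.** Section 10.4.2 calls its list of metrics open, and Section 10.4.1 refers procedures to an EEG Manual. This stands for matching of epoch counts, the scoring windows and the definition of SNR, and none of those gaps is raised here. It does not cover the peak rule, which the Protocol does name. An open list can add a measure but does not remove this one.
- **Section 4 says amplitudes, not peak amplitudes, and the word peak in Section 10.4.2 might qualify latency only.** That reading is possible. Even so, no other amplitude measure is given, so the text should be settled.
- **Nothing says that a larger P300 is better.** True. The study tests for differences from the wet reference, so the harm is a false or hidden difference, not a win for the noisier device. SNR, decodability and reliability may expose the noise, but they do not correct the amplitude contrast.
- **The sizes rest on assumed inputs.** True, including any assumption that a poorer device loses more epochs.

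A reader might also infer that the random draw of 25 to 35 deviants itself biases the device comparison. The documents do not support that. Nothing ties the draw to the device, the expected difference in count between devices is zero, and its standard error is about half a trial. The 1.46 dB figure describes the most extreme pair of runs, and it applies only if SNR is computed on the average, which the Protocol does not say. Nor would a fixed count remove the peak bias, since at 30 trials throughout the scored peak still rises with noise.

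**Conclusion.** The concern holds for peak scoring. As written, the P300 amplitude contrast depends on device noise as well as on the transmitted response, and the error runs towards larger scores for noisier averages. That direction needs only zero-mean noise. The size, about 13% for a 10 to 15 µV rise in noise SD and about 20% when usable trials also drop from 30 to 20, is illustrative and moves with the assumed amplitude, noise and search interval. Peak latency gains scatter from the same cause. The random trial count is a minor matter: it adds a little noise (CV of √n about 5%) to reliability and to any SNR based on the average, and it does not favour a device.

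**What to change.** In Section 10.4.2, under the P300 derived endpoints:

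- Score N100 and P3b amplitude as the mean voltage in a time window for each component. Fix the windows before any device results are seen and keep them identical for all devices and both visits.
- Keep peak amplitude as a descriptive measure only.
- Add a latency measure less sensitive to noise, such as fractional-area latency, at least as a sensitivity analysis.
- Leave the random count of 25 to 35 unchanged. Subsampling to a common number of clean epochs can be an optional sensitivity analysis. It should not be the main one, because it discards data, lets the worst recording set the count for the rest, and hides the yield of usable data, which is itself a device property and is already to be compared.

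The cost is a text change and analysis scripting, with no change to data collection. A window mean reads lower than a peak and is slightly less comparable with peak-based literature. It also depends on correct time alignment in every device, so stimulus timing should be checked before scoring.

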#### 10.4.1.4. Controlled artefact generation test

Participants are seated with EEG cap mounted and are instructed to sit still and relax. Prior to the recording, the EEG technician will explain the different actions to be completed during this task. During the task, participants are requested to perform voluntary movements (with the support of real time instructions displayed on the screen) that will generate artefacts in the EEG records. The movements will be following the sequence:

- resting with eyes open for 30 seconds
- eye blinking repeated ten times in 30 seconds when instructed. A cross appears at the screen center when the participant must blink.,
- controlled eye movement: following a moving target on a computer screen (horizontal and vertical saccades),
- jaw tightening and relaxing repeated ten times in 30 seconds when instructed. A cross appears at the screen center when the participant has to clench their jaw.
- three kinds of voluntary head movements, turning their head:
  - from right to left (alternating rotational without moving the chest), a ‘no’ gesture
  - from front to back without moving the chest (low amplitude movements), a ‘yes’ gesture
  - from front to back moving the chest, a ‘bowing’ gesture

All movement condition blocks within the controlled artefact session will be repeated such that two recorded blocks are available per conditions Between the repetition of the 5 movement conditions blocks (30 seconds of resting, eye blinking, controlled eye movements, jaw tightening and head movements), the participant will have one minute to rest freely as they wish.

#### 10.4.2. Outcome measurements

Data metrics to be included in the analysis may include but are not limited to the following.

##### Resting state EEG

##### Raw data

- Artefact free ongoing raw EEG activity during eyes open and eyes closed resting state conditions

##### Derived endpoints

- Absolute power and relative power averaged across artefact free time segments as well as connectivity (phase correlations and amplitude correlations) in different conventional frequency bands (e.g. IPEG guidelines, see table below)

| Band name                   | Delta | Theta | Alpha | Alpha 1 | Alpha 2 | Beta | Beta 1 | Beta 2 | Beta 3 | Gamma | Total |
|-----------------------------|-------|-------|-------|---------|---------|------|--------|--------|--------|-------|-------|
| Lower bound (included) [Hz] | 1.5   | 6     | 8.5   | 8.5     | 10.5    | 12.5 | 12.5   | 18.5   | 21     | 30    | 1.5   |

|                                |   |     |      |      |      |    |      |    |    |    |    |
|--------------------------------|---|-----|------|------|------|----|------|----|----|----|----|
| Upper bound
(excluded) [Hz] | 6 | 8.5 | 12.5 | 10.5 | 12.5 | 30 | 18.5 | 21 | 30 | 40 | 30 |
|--------------------------------|---|-----|------|------|------|----|------|----|----|----|----|

### Statistical analysis

- Univariate statistics and linear modelling to assess differences in derived endpoints between the test devices and the gold-standard clinical wet system across spectral frequencies.

- Correlational statistics (e.g. intra-class correlation) to assess test-retest reliabilities (D1 to D8) for derived endpoints for each device as well as univariate/resampling statistics to assess differences in test-retest reliabilities between devices.

- Multivariate analyses to decode eyes-closed from eyes-open resting state for each device as well as between the test devices and the gold-standard clinical wet system.

### **P300 ERP**

#### Raw data

- Time locked EEG responses, for frequent and infrequent tones.

#### Derived endpoints

- Peak latency and amplitudes of sensory (e.g. N100) and cognitive (e.g. P3b) evoked potentials from the auditory oddball task as well as topographic scalp distributions of the evoked components;

#### Statistical analysis

- Univariate statistics and linear modelling to assess differences in derived endpoints and scalp topographies between the test devices and the gold-standard clinical wet system.

- Multivariate analyses to decode frequent from infrequent tones for each device as well as a comparison of decodability of frequent and infrequent tones between the test devices and the gold-standard clinical wet system.

- Correlational statistics (e.g. intra-class correlation) to assess test-retest reliabilities (D1 to D8) for derived endpoints and scalp topographies for each device as well as univariate/resampling statistics to assess differences in test-retest reliabilities between devices.

### **Visual gamma-band stimulation**

#### Raw data

- Time locked EEG responses to the onset and offset of visual grating stimuli during artefact free data epochs.

#### Derived endpoints

- Time-frequency representations (TFR) of the spectral responses time-locked to the visual stimuli across a set of predefined frequencies (see Resting EEG above)

- Spectral response to visual stimulation in the gamma frequency band based on extant literature (~60-80 Hz)

#### Statistical analysis

- Univariate statistics and linear modelling to assess differences in derived endpoints and scalp topographies as well as differences in spectral responses between the test devices and the gold-standard clinical wet system.

- Correlational statistics (e.g. intra-class correlation) to assess test-retest reliabilities (D1 to D8) for derived endpoints and scalp topographies as well as spectral responses for each device as well as univariate/resampling statistics to assess differences in test-retest reliabilities between devices.

## **Controlled artefact stimulation test**

### **Raw data**

- Ongoing raw EEG activity segmented into data epochs of predominant artefact types

### **Derived endpoints**

- An analysis treating the artefact segments similar to Resting EEG will be performed (i.e. deriving average signal power and scalp topographies across the spectrum)
- Overall root-mean-square (RMS) signals during artefact periods
- Amount of data remaining after standard artefact cleaning

### **Statistical analysis**

- Univariate statistics and linear modelling to assess differences in derived endpoints and scalp topographies as well as differences in the amount of artefact free data between the test devices and the gold-standard clinical wet system.

## **10.5. Questionnaires and timing data**

### **10.5.1. Outcome measurements**

**All questionnaires are provided in Appendix 3 and an overview of the schedule of assessments for the questionnaires is provided in Figure P1.**

#### **Participant's questionnaires:**

- Entry questionnaire answers;
- Interim-before assessment questionnaire answers;
- Interim-after assessment questionnaire answers;
- Interim-after task questionnaire answers;
- Exit questionnaire answers.

#### **Staff questionnaires:**

- Post-training questionnaire answers;
- Interim clean-up questionnaire answers;
- Exit questionnaire at the end of a day answers;
- Exit questionnaire at the end of the study answers.

### **Set-up and clean-up timing**

- Time elapsed between the start of preparing an EEG system to the start of the first recording for each participant
- Time elapsed between the end of a recording session and a fully cleaned experimental set up for each participant

### **Statistical analysis**

For all quantitative questionnaires (VAS) as well as the timing data, univariate statistics and linear modelling to assess differences in ratings between the test devices and the gold-standard clinical wet system will be performed.

Summary overviews of overall preferred rank orders and answers to specific questions will be constructed.

### **10.5.2. Assessment Methods and Experimental Schedule**

Two sets of questionnaires will be used to assess the perception the experimenter and the participants had, of using or being participant to the EEG recording device using VAS as well as open question type assessments (Figure P1).

The experimenter will be asked to rate their expectancy on the equipment, the experimental set-up, the documentation and the level of burden associated with the set-up and cleaning of devices.

The participants will be asked to rate how comfortable they were during the experiment, the clarity of the instructions, and their experience of taking part in these assessments.

The testers will be asked to rate the level of clarity of the active tasks performed as well as the level of burden of the schedule of assessment.

Lastly information on the overall experience with the technology will be gathered.

## **10.6. Concomitant Medication and Illnesses**

### **10.6.1. Outcome measurements**

- Concomitant medication: date and time, name of medication;
- Concomitant illness: date, treatment (if any).

### **10.6.2. Assessment Methods and Timing**

Before a participant leaves the clinical site after the completion of the D1 Visit 1 assessments, the participant will be provided with a diary to collect any concomitant medication or illness during the 4 weeks of remote monitoring.

## **11. DATA MANAGEMENT AND STATISTICS**

### **11.1. Data entry and management**

#### **11.1.1. Data collection**

The results from evaluations conducted during the study will be recorded in an appropriate source data book for each participant. All supportive documentation submitted to the Sponsor must be clearly identified with the study or protocol number, and study participant's number; any personal information, including the study participant's name, must be removed or rendered illegible to preserve individual confidentiality.

Data from the on-site assessment tests will be collected by Biotrial and transferred to the Sponsor F.Hoffmann-La Roche for further analysis.

All the documents must be archived for a minimum of 15 years or according to the Sponsor's procedures, whichever is longer.

#### **11.1.2. Data validation**

Biotrial will be responsible for the on-site assessment data entry, and their validation (according to the Sponsor requirements).

## 11.2. **Statistical considerations**

The comparability of devices will be assessed using univariate statistics and linear modelling to test for significant differences in derived endpoints (e.g. absolute power) as well as appropriate statistics to assess comparability and stability (test-retest) questions (e.g. correlational statistics, intra-class correlations) where appropriate. Similar methods will be applied to questionnaire type data to generate an overall description of the comparability of device quality, comfort and ease of use in a multiparametric fashion.

## 13. APPENDICES

### Appendix 1: Regulatory and legal considerations

#### WMA DECLARATION OF HELSINKI – ETHICAL PRINCIPLES FOR MEDICAL RESEARCH INVOLVING HUMAN SUBJECTS

Adopted by the 18th WMA General Assembly, Helsinki, Finland, June 1964  
and amended by the:

- 29th WMA General Assembly, Tokyo, Japan, October 1975
- 35th WMA General Assembly, Venice, Italy, October 1983
- 41st WMA General Assembly, Hong Kong, September 1989
- 48th WMA General Assembly, Somerset West, Republic of South Africa, October 1996
- 52nd WMA General Assembly, Edinburgh, Scotland, October 2000
- 53rd WMA General Assembly, Washington DC, USA, October 2002 (Note of Clarification added)
- 55th WMA General Assembly, Tokyo, Japan, October 2004 (Note of Clarification added)
- 59th WMA General Assembly, Seoul, Republic of Korea, October 2008
- 64th WMA General Assembly, Fortaleza, Brazil, October 2013

